## **2.9 Early termination of the investigation**

The Sponsor may terminate the investigation prematurely according to certain circumstances, for example:

- Ethical concerns
- Insufficient subject recruitments
- More than 5 patients with two episodes of severe hypoglycaemia ( $\leq 2.2$  mmol/l) in the intervention group
- 10 device deficiencies that prevent the use of GS2 for 4 hours
- Changes in accepted clinical practice that are too large and make it unwise to continue the investigation
- Early evidence of benefit or harm of the experimental intervention
- Root mean square (RMS) prediction error of GS2 is greater than 26% for predictions of BG 2 hours into the future (see point 3.4 for rationale)

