### 5.3 Other Outcomes of Interest

Workload:

- Frequency of daily and cumulated BG measurements per patient and in the cohort during the patient's enrolment period (duration of the ICU stay with a max of 15 days).
- Frequency of daily and cumulated adjustments of insulin and nutrition pump settings during the patient's enrolment period.

Compliance (only in intervention arm)

- Number of episodes per patient and in the cohort where a BG measurement is not followed up within 30 minutes by an accepted GS2 advice (during the enrolment period)
- Number of episodes per patient and in the cohort where GS2 advice was accepted by the nurse but pumps were not set according to the advice within 30 min by the nurse (nurse did not notice, was too busy, forgot, or misinterpreted advice = true errors)
- Number of advices given by GS2 which were accepted, accepted with modification or rejected

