### 5.4 Safety Outcomes

Hypoglycaemia

- Overall number and percentage of mild ( $\leq 3.2$  mmol/l), and severe ( $\leq 2.2$  mmol/l) hypoglycaemic events per patient and in the study.
- Number and percentage of mild ( $\leq 3.2$  mmol/l), and severe ( $\leq 2.2$  mmol/l) hypoglycaemic events due to non-compliance (only in intervention arm)

Hyperglycaemia ( $> 8.5$  mmol/l)

- The time taken to normalize blood glucose will be the time from enrolment in the study to the time of the first of two consecutive BG measurements  $\leq 8.5$  mmol/l

- Percentage of time in the ICU with hyperglycaemia (BG > 8.5 mmol/l) before and after normalization per patient and in the cohort.
- Percentage of time in the ICU with hyperglycaemia (BG > 8.5 mmol/l) before and after normalization per patient and in the cohort due to non-compliance (only in intervention arm)
- Number of hyperglycaemic episodes after normalization per patient and in the cohort
- Number of hyperglycaemic episodes after normalization per patient and in the cohort due to non-compliance (only in intervention arm)

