## **8.3 Compliance with clinical investigation intervention**

Some strategies to improve adherence to the use of GS2 will be made.

**Training:** All caregivers will participate in training sessions before the beginning of the study. They will also receive a summary brochure with the main information. During the trial a clinical investigator will come daily to see if the caregiver has any question and if there is a need for a one-to-one training.

**To do list:** GS2 contains a "To do list" as a reminder for the caregivers to use the system. The non-compliance will not be analysed while the study is underway. The rate will be analysed at the end of the study as a secondary outcome and will be defined as:

- Number of episodes per patient and in the cohort where a BG measurement is not followed up within 30 minutes by a request for GS2 advice.
- Number of episodes per patient and in the cohort where pumps were not set within 30 min according to a GS2 advice accepted by the nurse (nurse did not notice, was busy, forgot, or misinterpreted advice = true errors)

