### **9.2.4 Assessment of safety outcomes**

#### Hypoglycemia

- Overall number and percentage of mild ( $\leq 3.2$  mmol/l) and severe ( $\leq 2.2$  mmol/l) hypoglycaemic events per patient and in the cohort
  - All hypoglycaemia episodes will be reported in the eCRF, number and percentage will then be calculated.

- Number and percentage of mild ( $\leq 3.2$  mmol/l) and severe ( $\leq 2.2$  mmol/l) hypoglycaemia events due to non-compliance (only in intervention arm)
  - o All hypoglycaemia episodes will be reported in the eCRF. Then, those data will be analysed jointly with the “non-compliance” outcomes.

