## 10.3 Documentation and reporting in Medical Device Category C clinical investigations

**Device deficiencies** and all **adverse events (AE)** including all **serious adverse events (SAE)** are collected, fully investigated and documented in the safety report form and appropriate CRF during the entire investigation period, i.e. from patient's informed consent until the last CIP-specific procedure, including a safety follow-up period.

- Documentation of AEs (including SAEs) by the PI includes diagnosis or symptoms, start and stop

dates of event, event treatment, event resolution, assessment of seriousness and causal relationship to MD and/or investigation procedure (Art. 32 ClinO-MD, ISO14155) [2, 4].

- Documentation of DDs by the PI includes description of event, start date, investigational device information, action taken regarding the investigational device, and whether the DD led to an AE. The Sponsor shall review all DDs and determine and document in writing whether they could have led to a SAE (DD with SADE potential) (Art 32. ClinO-MD, ISO14155) [2, 4].

The Sponsor provides the CA and the CEC with the documentation at their request (Art. 32 ClinO-MD) [4]. AEs which can be linked with the study (see point 10.3.1) will be assessed during the daily visit.

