| 
2) Advice that gives rise to concern:
 
Examples:
 

- Insulin dose (<math>> 0</math> U/h) is advised when blood glucose is below target (5 - 8.5 mmol/l) and the patient is not insulin-dependent chronically diabetic.

- Glucose bolus injection is advised when patient's blood glucose is not hypoglycaemic.

- No nutrition advised for a patient on the fourth day in the ICU.

- GS2 advises to increase insulin in a single step larger than 2 U/h.

 | 
Refuse the advice given by GS2 until the PI or co-investigators have been consulted.
 
Take a note of the situation (which patient, date & time of the observed behavior, description of the behavior, screenshot of GS2 and of the advice window).
 
Contact the investigator immediately, not later than 12 hours after the observance.
 
The PI will decide if it is a device deficiency and if a suspension of the study is required.
 |
| 
3) Slow performance
 
Examples:
 

- Waiting time after a requested advice exceeds 20s until advice window opens.

                                                                                                                                                                                                                                                                                                                                                                    | 
Slow performance can be expected if a large amount of data of the patient has to be loaded, but it could also be either a device deficiency, or a failure of the external patient data management system Clinisoft.
                                                                                                                                                                                                                                                 |

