| 
 
- Waiting time to load a new patient from Clinisoft exceeds 2 minutes.
 
 
Waiting time for "Nutritional Targets" page, "Advice" Page, and "Patients" page exceeds 30s
                                                                                                                                                                                                                                            | 
Take a note of the situation (which patient, date & time of the observed behavior, description of the behavior, screenshot of GS2 if possible). Please add a description of how you interacted with GS2 and what the approximate time of waiting was.
 
The user should discuss the note with one of the investigators during the daily visit.
 
The PI will decide if it is a device deficiency.
 |
| 
4) Malfunction/technical issues:
Examples:
 
 
- Import of the patient's data from Clinisoft is incomplete (data shown in Clinisoft are not visible in GS2)
 
- Data "out-of-range" messages appear when entered data are correct, for example "75 kg is not a correct body mass"; "2345 kcal is not a correct energy expenditure"
 
- Graphical user interface freezes and inhibits use of GS2
 
 | 
The user should stop using GS2 until the investigator has been informed.
 
Meanwhile, take a note of the situation (which patient, date & time of the observed behavior, description of the behavior, screenshot of GS2 if possible).
 
Contact an investigator immediately.
                                                                                                                      |

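### The 30-minute non-compliance rule has no exemption for times when GS2 is unavailable or users are told not to follow it, so device downtime can be counted as user non-compliance

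*Protocol*

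**What the plan says.** **Outages are foreseen.** Protocol 2.9 lists among the reasons for early termination "10 device deficiencies that prevent the use of GS2 for 4 hours"; section 1.6 has the same criterion. Nine such deficiencies would not meet it.

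**Users are told not to use GS2, or not to follow it, in defined situations.** In the table in 10.3.2, the instruction for a malfunction or technical issue is: "The user should stop using GS2 until the investigator has been informed". For advice that gives rise to concern it is: "Refuse the advice given by GS2 until the PI or co-investigators have been consulted".

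**Non-compliance is defined in two ways.** In 8.3, and in the same terms in the synopsis and 9.2.3, an episode is one where "a BG measurement is not followed up within 30 minutes by a request for GS2 advice". In 5.3 it is one where "a BG measurement is not followed up within 30 minutes by an accepted GS2 advice". Neither mentions GS2 being unavailable.

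**The count feeds safety outcomes.** Section 5.4 includes the number and percentage of "hypoglycaemic events due to non-compliance (only in intervention arm"), with parallel items for hyperglycaemia. Section 9.2.4 gives the method for hypoglycaemia: "All hypoglycaemia episodes will be reported in the eCRF. Then, those data will be analysed jointly with the" non-compliance outcomes. The hyperglycaemia items are handled the same way. No link to the device-deficiency log is stated.

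**Deficiencies are recorded separately.** Section 10.3 says: "Documentation of DDs by the PI includes description of event, start date, investigational device information", followed by the action taken and whether the deficiency led to an adverse event.

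**The concern.** A nurse who follows 10.3.2 after a malfunction makes no request for advice and is scored non-compliant under both wordings. A nurse who follows 10.3.2 and refuses advice of concern is scored under the 5.3 wording. The rule therefore counts conduct that the protocol itself instructs, and counts device downtime as a lapse by the user.

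The trial is meant to validate the safety of a device that the protocol says has had no clinical testing. The outcomes attributed to non-compliance exist to show which glycaemic events arose because GS2 was not followed. If events during device failure enter that category, the split between device and user errs in the device's favour. Expected numbers are small, so a single event could alter how the split reads.

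**Working it through.** **Inputs**

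- Outage length: 4 h = 240 min (1.6, 2.9).
- Response window: 30 min (synopsis, 5.3, 8.3, 9.2.3).
- Glucose-measurement interval under the local protocol: 2 h when stable, 15 to 30 min after insulin is started until stable (8.1.2).
- Readings per patient: about 40 on average (3.7, 8.1.1).
- Intervention group: 71 patients (11.2).

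**The plan's own figures.** Section 3.7 gives the risk of hypoglycaemia per patient as 0.05% × 40 = 2%, which reproduces. Over the intervention group, 2% × 71 = 1.42, so about 1.4 patients. The sample size also reproduces: a difference of 10 points, SD 21, two-sided 5% and 80% power give 70.2 per group from the t distribution, rounded up to 71. Nothing below depends on the sample-size calculation.

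**Step 1: the rules side by side**

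| Situation | Instruction in 10.3.2 | Scored if a request is needed (synopsis, 8.3, 9.2.3) | Scored if acceptance is needed (5.3) |
|---|---|---|---|
| Malfunction, GS2 not usable | Stop using GS2 | Yes | Yes |
| Advice of concern | Refuse it pending consultation | No, a request was made | Yes |
| Reading in the last 30 min before GS2 returns | None | Not necessarily | Not necessarily |

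**Step 2: share of an outage that is exposed.** A reading cannot be followed in time if it falls more than 30 min before GS2 returns:

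(240 − 30) / 240 = 210 / 240 = 87.5%, about 88%.

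**Step 3: readings scored per affected patient per 4-hour outage**, as 210 min divided by the interval:

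- 2-hour interval: 210 / 120 = 1.75
- 30-minute interval: 210 / 30 = 7
- 15-minute interval: 210 / 15 = 14

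**Step 4: share of all readings in the intervention group.** The total is about 71 × 40 = 2840. Take nine outages, one short of the criterion. The number of patients per outage is an assumption.

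| Interval | Readings scored, 1 patient per outage | Share of 2840 | Share, 5 patients per outage |
|---|---|---|---|
| 2 h | 9 × 1.75 = 15.75 | 0.6% | 2.8% |
| 30 min | 9 × 7 = 63 | 2.2% | 11.1% |
| 15 min | 9 × 14 = 126 | 4.4% | 22.2% |

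The lower rows are upper bounds, because the local protocol uses those intervals only until glucose is stable.

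**Step 5: where an event goes.** Suppose hypoglycaemia occurs during an outage. Under 5.4 and 9.2.4 it is analysed jointly with the non-compliance count, which contains the readings around it. Under 10.2 and 10.3 it is also rated for relation to the device and noted on the deficiency record. The protocol does not say which classification governs, or that the two must be compared.

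**The case against.** The strongest reply is that this is a descriptive adherence count in one arm, listed in 5.3 among other outcomes of interest, and that device attribution runs on its own track. That track exists and limits the point. Several stronger readings are tempting, and the protocol does not support them.

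- *Harm during a failure is charged to the nurse and not to the device.* A reader might infer this. But 10.3 records whether a deficiency led to an adverse event, 10.2 rates each event for relation to the device, 10.3.2 has serious device effects and deficiencies listed in the annual safety report, and 5.4 counts all hypoglycaemic events whatever their cause. An event is not lost from the device's record; it may appear under conflicting labels.
- *Outages inflate a count of user errors.* The true-errors wording belongs only to the separate item on pumps not set after accepted advice.
- *Every reading in an outage is scored.* Readings in the last 30 minutes may still be followed in time.
- *The outage window cannot be recovered.* Section 10.3 names only a start date for deficiencies, whereas it asks for start and stop dates for adverse events. But its list need not be exhaustive, the opening of section 10 asks for resolution, and the 4-hour criterion itself requires the duration to be known. What is missing is a stated requirement for end times precise enough to match a 30-minute window.
- *One patient could accumulate 20 to 160 misclassified readings.* That is 40 hours of downtime at 2-hour to 15-minute intervals, and puts one patient in all ten outages. The plan assumes about 40 readings per patient in total.

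It is also fair to say that joint analysis is not an automatic assignment of every event to non-compliance, and that a statistical analysis plan, not shown, could define the attribution. But the protocol fixes the definition of a non-compliance episode itself, in four places, without an exemption. That part of the concern stands.

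**Conclusion.** The concern holds in limited form. As written, the 30-minute rule scores device downtime and instructed non-use as non-compliance and, under 5.3, instructed refusal as well. Glycaemic events in those periods can then enter the intervention-arm outcomes attributed to non-compliance while being recorded as device-related elsewhere, with no rule to reconcile the two.

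The size is about 88% of a 4-hour outage, or 1.75 to 14 readings per affected patient per outage. This assumes that measurement during an outage follows the local protocol's intervals. It also assumes that those readings reach the GS2 database, from which 9.2.3 takes the count; the protocol does not say whether readings taken during downtime are imported later. The number actually misclassified is therefore uncertain. With only about 1.4 intervention patients expected to have hypoglycaemia, one misattributed event could still change the device-versus-user reading.

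Overall hypo- and hyperglycaemia counts, adverse-event causality ratings and the intention-to-treat comparison of time in target are not affected. A reader might infer a bias in favour of GS2 in the comparison between arms; the documents do not support that. The possible bias is confined to the split of events within the intervention arm.

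**What to change.** 1. In 5.3, 8.3 and 9.2.3, and in the matching synopsis entry, exclude from the non-compliance counts any period of documented GS2 unavailability and any non-use or refusal instructed under 10.3.2.
2. In 5.4 and 9.2.4, report hypo- and hyperglycaemia in those windows as a separate category, *during device deficiency*, linked to the deficiency log.
3. In 10.3, require start and end date-time for each deficiency.
4. Use one definition, request or acceptance, throughout.

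The cost is one extra field on the deficiency form, small text edits and a little more analysis work. No extra patients or procedures are needed, and the sample size stays at 71 per group.

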## **2.10 Clinical investigation plan amendments**

Substantial amendments are only implemented after approval by the CEC (Art. 15 ClinO-MD) [4] and after approval by the CA also (Art. 20 ClinO-MD) [4]. The use of waivers from the CIP is prohibited (Annex XV, Chapter 2, Art. 3.10 MDR).

Under emergency circumstances, deviations from the CIP to protect the rights, safety and well-being of the subjects may proceed without prior approval by the Sponsor, the CEC and the CA. Such deviations shall be documented and reported to the Sponsor, the CEC and to the CA within 2 days (Art. 34 ClinO-MD) [4].

All non-substantial amendments are communicated to the CEC together with the Annual Safety Report (ASR) (Art. 15 ClinO-MD) [4], and for category C clinical investigations to the CA as soon as possible (Art. 20 ClinO-MD) [4]. The ASR shall include any deviations from the CIP that may have affected the rights, safety or well-being of the subject or the scientific integrity of the investigation (ISO14155) [2].

## **2.11 Deviation from the Clinical Investigation Plan**

The use of waivers from the CIP is prohibited. Investigator is not allowed to deviate from the CIP, except

as specified in point 2.10. All deviations occurring will be followed in the deviation log.

### **3. BACKGROUND AND RATIONALE**

#### **3.1 Background and Rationale for the clinical investigation**

The survival and the outcomes of critically ill patients are strongly influenced by the management of insulin therapy and the nutritional support. All improvements in these care processes and specific therapeutic interventions result in a decreased ICU morbidity and mortality rate [9-11]. Hypo- or hyperglycaemia are related to higher mortality, especially in non-diabetic patients [12, 13]. An association between high blood glucose (BG) variability and increased infection rates and mortality were also observed [14, 15]. In addition, inadequate nutritional support may also contribute to protein loss and muscle wasting, which may lead to post-ICU weakness [16-18] and to a further increase of the ICU and post-ICU morbi-mortality [19-21]. These ICU neuromuscular complications worsen the general clinical outcomes, and are linked to an increased mortality, persistent functional limitations, and cognitive impairment. The reported incidence varies between 25 and 100% [6].

International professional societies have published evidence-based guidelines for BG control and nutritional support for ICU patients [22-24], but their implementation and the adherence to local guidelines remains very challenging. Implementing BG control to local guidelines showed a low 50% adherence [25, 26] and despite nutritional recommendations, patients staying more than 72 hours in the ICU observed in a multicenter study received on average less than 60% of their estimated energy expenditure [27].

The Glucosafe 2 (GS2) software is a decision support system intended to help caregivers in achieving optimised BG control coupled to nutritional support. It is based on a mathematical model of the glucose-insulin metabolism. This model integrates the following data: body mass (BM), age, gender, type of diabetes, renal replacement therapy, serial blood glucose measurements, insulin therapy and the nutrition support (including non-nutritional calories). Based on these data, GS2 can calculate the patient's insulin sensitivity and recommends the dose of insulin and nutrition required for each ICU patient.

This model should allow a meticulous glycaemia control and a diminution of glycaemia variability as well as the reduction of deleterious hyper- or hypoglycaemia events. Furthermore, the GS2 model allows to a certain degree to compensate cumulated energy and protein deficits after prolonged acute illness with high catabolism. In addition, GS2 provides information to supplement nutritional proteins by complementary amino acid perfusions in order to reach the protein target.

This pilot study aims to evaluate if the use of the GS2 software can increase the quality of the glucose control ("time-in-target", stability of blood glucose, decrease of hyper- hypoglycaemia events) as well as the quality of nutrition therapy (reaching of energy and protein targets, decrease of energy and protein debts) in comparison with the actual local protocols.

#### **3.2 Identification and description of the Investigational Medical Device**

The name of the investigational product is GS2. The GS2 software is a class IIb decision support system. The version used in the protocol is release 1.0, GMDN code: 61087. The manufacturer is Aalborg University, Aalborg, Denmark. GS2 is not commercially available and is not CE-marked.

GS2 software is a medical device, which for the purpose of the clinical investigation will be installed at the bed-side computer running Centricity, which is the electronic Patient Data Management System (ePDMS) used in the ICU-Geneva. GS2 is not in physical contact with the patient, nor is it connected with other devices that are in physical contact with the patient (e.g. infusion pumps).

The GS2 system is designed to provide:

- 1) On-demand open-loop advice for personalized insulin therapy to regulate blood glucose in adult ICU patients based on predictions of the patient's BG using a physiological model of glucose and insulin pharmacodynamics, gastrointestinal absorption of nutrients and insulin release.
- 2) An overview of the glycaemic and nutritional history and current status of adult ICU patients through information automatically retrieved from the ePDMS and the GS2 database.
- 3) On-demand open-loop advice for setting of personalized nutrition targets and for achieving the

caloric and protein targets.

- 4) Balancing of insulin dosing and nutritional targets against each other.
- 5) Supporting the clinical workflow by maintaining a “To Do” list of upcoming tasks.

**Indication:** GS2 is intended for use in adult ICU patients fasting or on enteral and/or parenteral nutrition. In patients with neurological trauma, GS2 will increase the threshold for hypoglycaemia to safeguard the patients against cerebral hypoglycaemia.

**Contraindications:** GS2 is not intended for patients on oral feeding or pregnant patients.

Detailed criteria for inclusion/exclusion are given in sect. 7.1.

The device is intended for use by physicians and nursing staff trained in the use of GS2. The caregiver can accept or reject the advice (“open-loop advice”), mitigating issues of safety and effectiveness.

GS2 is not intended to monitor the performance of the insulin and nutrition pumps.

